## 5. Study Aim

The aim of the study is to establish the safety profile, assess the community acceptance, and weigh the economic advantages of a three-agent MDA combining azithromycin, albendazole (Alb), and ivermectin (Ivm) in comparison to the standard MDA regiment which separates the administration of azithromycin from the dually administered ivermectin and albendazole by a period of two weeks.

### 5.1. Specific objectives

#### 5.1.1. **Primary Objective:**

To establish the safety profile, assess the community acceptance, and weigh the economic advantages of a three-agent MDA combining azithromycin, albendazole (Alb), and ivermectin (Ivm) in comparison to the standard MDA regiment which separates the administration of azithromycin from the dually administered ivermectin and albendazole by a period of two weeks.

#### 5.1.2. **Secondary Objective:**

- Understanding the perceptions of the beneficiaries receiving the co-administration of azithromycin, ivermectin, and albendazole especially surrounding pill burden and the change in MDA distribution schedule.
- Understanding the perceptions of the co-administration strategy by the local health workforce as a means of PC-NTD drug delivery.
- A cost analysis comparing existing MDA unit costs from woredas within the region already on a standard MDA schedule with that of the co-administered woredas.
- A literature/data review across 19 different countries including Ethiopia which will analyse the possible benefits of co-administration from an economic and epidemiological standpoint when compared with current trends towards achieving 2020 NTD control and elimination goals.

## **6. Description of the Study Area**

The directly observed MDA by co-administration of azithromycin, IVM and ALB will take place within the woreda of Kofele in the West Arsi Zone of Oromia in region. This woreda has an estimated population of people. Within this population, the study requires a total of 13,680 individuals with 6,840 in each arm. The study will target a population of 16,000 people which will allow a 15% cushion to factor in non-compliance and exclusionary criteria among the recipients. This woreda was selected due to the co-endemicity of LF and trachoma.

### **6.1. Kofele woreda**

#### **6.1.1. General information**

Kofele is one of 17 woredas in West Arsi Zone in Oromia region of Ethiopia. West Arsi is bordered on the south by the Sidama Region and the SNNPR, on the west by the SNNPR, on the northwest by East Shewa Zone, on the northeast by the Arsi Zone, and on the east by Bale Zone, and on the Southeast by Guji zone. The administrative center of the zone is in Shashemane. Kofele woreda is 27 KMs southeast from Shashemane, at an elevation of 2695 meters above sea level. Based on the 2014 E.C. estimate by FMOH the woreda has a population of 251,098.

#### **6.1.2. Kofele NTD prevalence and treatment history**

Kofele has a prevalence of 27.3% for trachoma folliculitis, 1.5% for LF. The woreda is currently under annual treatment schedule for LF and trachoma. This will be the fifth round of trachoma MDA conducted in the woreda.

## 7. Participant Selection Criteria

Standard FMOH criteria for individual agent MDA will be used to determine eligibility of individuals to receive each drug. Individuals eligible to receive all three agents, 'co-administration', will be enrolled in the study.

### 7.1. Inclusion Criteria

- Must have been residing in the community for at least three months;
- Eligible to receive all three agents according to standard MDA criteria;

### 7.2. Exclusion Criteria

- Not eligible to receive one or more drugs according to standard MDA criteria;
- Less than 5 years of age (not eligible for ivermectin)\*\*
- Pregnant women (azithromycin only, not eligible for albendazole and ivermectin)
- Lactating women (Only administered azithromycin and albendazole, not eligible for ivermectin);
- History of allergies to the drugs being studied (azithromycin, ivermectin, albendazole)
- Those who refused to be part of the study (will be addressed via the normal MDA schedule if they prefer with initial treatment with IVM/ALB and azithromycin treatment two weeks later)
- Residents who cannot swallow tablets;

*\*\*Note that patients that are not eligible for IVM, will receive azithromycin and albendazole. Patients that receive azithromycin and albendazole will be followed up through the same procedure as the triple drug therapy to try to track any AEs attributed to the two drug combination.*

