| Study Duration     | 6 months                                                                                                                                                                                                                                                                                                                                                                                                                                                                                                                                                                                                                                                                                                                                                                                                     |
| Interventions      | All residents of the selected communities will be invited to participate in the co-administered drug treatment strategy. Consenting/assenting residents of the villages will be screened as per the inclusion and exclusion criteria. Dosage and treatment age groups will follow WHO protocols for lymphatic filariasis, onchocerciasis, STH,  and trachoma  . Study enrolment will continue until the sample size is attained.                                                                                                                                                                                                                                                                                                                                                     |
| Number of subjects | A total of 16,000 people: 8,000 people in the trial arm and 8,000 in the study arm. If there is no increase in adverse events in the trial arm, triple-drug therapy will be used to treat the remaining 4-5,000 people in the district.                                                                                                                                                                                                                                                                                                                                                                                                                                                                                                                                                                      |

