## 2. **Modes of Action of the study drugs and their administered dosage**

### Azithromycin

After ingestion, azithromycin spread quickly and widely through the body. While albendazole and ivermectin are primarily absorbed by the plasma in the human body, azithromycin is found in much higher levels (as much as 50 times) in the tissue. It is also absorbed by immune cells such as phagocytes which help to transport it to sources of infection. Azithromycin is intracellularly active which help explains its efficacy against bacteria such as *C. trachomatis*.

For mass drug administration in Ethiopia, Zithromax is given as a single observed dose, determined by dose pole as per WHO recommendation. Everyone 5 years and older receives their dose in 250 mg tablets while children between 6 months and 5 years old will receive syrup (200 mg per 5 ml). Individuals aged 6 months and under as well as pregnant women are offered topical tetracycline.

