## 8.2. Awareness Creation, Community Mobilization Mechanism, and Training

The roll-out will begin with a joint TOT in Addis led by the FMOH, AHRI and LSHTM. Each study team will include medical and public health professionals experienced in clinical trials and NTD MDAs. The TOT will be an opportunity to review the training modules, assess the monitoring plan, and establish agreed upon courses of action for predictable eventualities.

Note that before the study begins, the FMOH and appropriate RHBs will work with the zonal and woreda-level offices where the study will take place to ensure full understanding and compliance with the study parameters. It is important to note that the communities in Kofele district will be excluded from the usual MDA training cascade which begins at the regional level and then descends down the zonal, woreda-level, and kebele-level tiers where Health Extension Worker (HEW) and Health Development Army (HDA) are the final training recipients. In place of this cascade, the FMOH/AHRI/LSHTM team will provide protocol specific training to the woreda health officers and the health extension workers. The training modules will include an overview of the national NTD training manual followed by an in-depth explanation of the study protocol and how it differs from the common MDA procedure. Training modules that will be modified from the usual NTD training will include:

- Given the possible pill burden of co-administration (up to nine pills for an adult), HEWs will be taught to allow beneficiaries a maximum swallowing regiment (two pills, swallow, two pills, swallow) in order to discourage rushed administration and any possibility of choking. HEWs will be taught to encourage patients to take one pill at a time if they prefer.
- The study team will train the HEWs and Woreda Health Officers on the protocol for reporting to the local medical team that will be stationed nearby during the study.
- The FMOH and the study team will create a mobilization plan with the HEWs that will rely on the Health Development Army and local leaders to create awareness of the study which in turn will help ensure participation. This will enable the project to get a collective informed consent for the activity by the community.

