## 11 Secondary Outcomes

- I.) **Better understand the perceptions of the beneficiaries/recipient population of co-administration of azithromycin, ivermectin, and albendazole especially surrounding pill burden and the change in MDA distribution schedule.**

**Background:** Currently, mass drug administration takes place through three distinct phases depending on the number of NTDs for which a woreda is endemic. Assuming a community is endemic for trachoma, LF, and OV, the first MDA round that takes place addresses OV and LF through a height-dependent dosage of up to four pills of ivermectin and, regardless of height or age, one pill of albendazole. The second round of MDA takes place two weeks later for the administration of azithromycin involving a height-dependent dosage of up to four pills for azithromycin (with TEO administered to children under a height of 48 cm). According to the Ethiopian national strategy to eliminate onchocerciasis, almost all of the OV endemic woredas in Ethiopia have been moved to a twice-a-year treatment strategy. Notably, though STH and SCH are usually treated through school-based MDA, communities that are co-endemic for STH with prevalence over 50% and IVM will receive a second round of albendazole (or mebendazole) together with the OV second round of ivermectin.

**The Challenge:** While cost, supply chain, and the work load of the local health work force are important considerations (and further explored through the other secondary outcomes of the study in this section), the most important aspect to consider is that of the beneficiary. Depending on the dosage, determined by a beneficiary's height for ivermectin and azithromycin, an adult of certain height will find him or herself taking up to nine pills (four for ivermectin, four for azithromycin, and one for albendazole). While the swallowing regiment (a maximum of two pills at a time or one at a time according to the beneficiaries' comfort level) is meant to control for the possibility of choking during MDA, taking up to nine pills at one time can create both physical and mental duress. The level of duress, if any, must be ascertained and considered in conjunction with the physiological assessment of side effects and the operational benefits before any adoption of the co-administration strategy can take place by a national program.

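### Sections 2 and 7.2 give pregnant women different trachoma treatments, and the double-asterisk note in 7.2 overlooks the tetracycline rule for infants of 6 months and under

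*Protocol*

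**What the plan says.** Three statements in the Protocol bear on residents who are not enrolled in the trial but are still treated.

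- Section 7.2 (Exclusion Criteria) includes the bullet "Pregnant women (azithromycin only, not eligible for albendazole and ivermectin".
- Section 2 (Azithromycin), on practice in Ethiopia, says "Individuals aged 6 months and under as well as pregnant women are offered topical tetracycline". The sentence before it says that "children between 6 months and 5 years old will receive syrup (200 mg per 5 ml".
- A note marked with a double asterisk closes section 7.2: "Note that patients that are not eligible for IVM, will receive azithromycin and albendazole". The mark sits on the bullet for children under 5 years, which has no lower age limit. The note adds that people given these two drugs are followed up for adverse events in the same way as the triple-drug group.

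Two general rules stand behind these. Section 7 says "Standard FMOH criteria for individual agent MDA will be used to determine eligibility of individuals to receive each drug", and the Study Protocol Summary says "Dosage and treatment age groups will follow WHO protocols for lymphatic filariasis, onchocerciasis, STH" and trachoma. Under section 8.2, field staff are trained through "an overview of the national NTD training manual followed by an in-depth explanation of the study protocol".

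**The concern.** A protocol that treats people outside the trial should give each group one treatment. Here a pregnant woman is assigned an oral antibiotic in one section and an eye ointment in another. An infant of 6 months or under is assigned ointment in one section and two oral drugs in another.

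What is at stake is patient safety at the distribution point and the composition of the two-drug follow-up group. A health extension worker who applied the note as written would give azithromycin and albendazole to infants for whom section 2 specifies ointment. Those infants would then also enter the two-drug adverse-event follow-up. The main analysis is not at stake.

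**Working it through.** No figure in the plan depends on this point, so there is nothing to recompute. The check sets the texts side by side.

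| Group | Section 2, Azithromycin | Section 7.2, own bullet | Section 7.2, double-asterisk note | Result |
|---|---|---|---|---|
| Pregnant women | Topical tetracycline | Azithromycin only; no albendazole, no ivermectin | Not marked on this bullet; general wording would give azithromycin and albendazole | Section 2 and the bullet contradict each other |
| Infants of 6 months and under | Topical tetracycline | Covered by the under-5 bullet | Azithromycin and albendazole | Note contradicts section 2 |
| Children over 6 months and under 5 years | Azithromycin syrup | Covered by the under-5 bullet | Azithromycin and albendazole | No conflict on azithromycin; section 2 states no age limit for albendazole |
| Lactating women | Not mentioned | Azithromycin and albendazole | Same two drugs | No conflict |

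**Step 1: pregnant women.** Section 2 describes national practice. Section 7 makes the standard ministry criteria the rule for each drug, and the exclusion list in 7.2 applies those criteria. The two sections should therefore describe the same rule, but one gives ointment and the other azithromycin. Deferring to the ministry criteria shows that one statement must be wrong without showing which.

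**Step 2: infants.** This conflict needs no stretched reading. The note is attached to the under-5 bullet, that bullet has no lower age limit, and the note makes no exception. Infants of 6 months and under therefore fall inside it, while section 2 assigns them tetracycline.

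**Step 3: the note and pregnancy.** The note's wording covers everyone who cannot take ivermectin, which would include pregnant women. However, the mark is on a different bullet, and the adjacent pregnancy bullet bars albendazole expressly. The specific rule should govern. This is untidy drafting, not a further treatment rule.

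**Step 4: reach.** Section 7 enrols only people eligible for all three drugs. Neither group can contribute to the primary adverse-event comparison, so the sample size, the 1.5% margin and the test are untouched.

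**The case against.** The strongest reply is that section 2 is background and section 7.2 is the operative text. Dosing and eligibility are referred to WHO and ministry criteria. Health extension workers already give azithromycin in routine rounds, and their training starts from the national manual. Experienced staff may well treat these groups correctly whatever the protocol says. Most of this stands, and it is why the point is minor. It does not remove the contradiction, because the protocol describes the same external standard in two ways and the same training goes on to explain the protocol in depth. One might also say that tetracycline is merely offered in pregnancy as an alternative. Section 7.2 mentions no alternative, though, and section 2 groups pregnant women with the infants who get ointment.

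Several stronger readings are tempting, and the documents do not support them.

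- A reader might infer that the note directs albendazole to pregnant women, and so count a third treatment for them. That requires detaching the note from its marker and overriding the adjacent bullet.
- A reader might cite section 11, "with TEO administered to children under a height of 48 cm", as confirming the infant rule. It gives a height, and nothing in the protocol equates 48 cm with 6 months. It also says nothing about pregnancy.
- A reader might infer from the contraindication checklist, which ends only in an inclusion decision, that the drugs given would go unrecorded. The treatment form in Appendix 3 has a separate tablet count for each drug, and Table 4 lists a study drug registry completed on distribution day. The forms do not show whether people who are not enrolled complete them, so no recording gap is established.

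**Conclusion.** The point holds as a minor wording error with a patient-safety aspect. One of the two statements on pregnancy is wrong, and the note is wrong for infants of 6 months and under if section 2 describes the standard correctly. Which treatment in pregnancy is correct depends on ministry criteria that are not in the documents, so this review does not choose between them.

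The effect on the primary comparison is none. No number of people affected can be given, because the protocol states neither how many residents are pregnant nor how many are infants. A reader might tally conflicts across the groups who cannot take ivermectin, but the protocol defines no closed list of such groups. Section 7.2 also excludes residents who cannot swallow tablets, for example, so a ratio would mean nothing. A reader might also infer that people will be wrongly dosed. The documents show conflicting instructions, not that outcome.

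**What to change.** Make two changes before field training.

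1. Reword the note in section 7.2 along these lines: *Persons not eligible for IVM who are eligible for both azithromycin and albendazole under standard MDA criteria will receive azithromycin and albendazole; this does not apply to pregnant women or to infants of 6 months and under.* Lactating women and older under-5s who qualify stay covered, and the two-drug follow-up group is then properly defined.
2. Have the clinical leads check the ministry criteria for pregnancy, then state the same treatment in section 2 and in the pregnancy bullet of section 7.2.

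There is no statistical cost. The revision history records approval by the AHRI/ALERT ethics committee, so changing treatment wording may need notification or a short amendment. That is the only real burden.

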## 8.8 Co-Administration Schedule

*The study will have two cohorts control arm, which will receive the usual MDA, and study arm which will receive the triple co-administration. Each arm will have approximately 6,800 people, 42 Gotes. Primarily, the clustering will be made by geography where 42 adjacent Gotes will be in one and the other 42, in another. Which cluster will be the control or study arm will be decided by simple lottery method.*

*After decision on the study arms, the study team will conduct the training and the actual co-administration for a 17-day period (three days for training and 14 days for actual co-administration and surveillance). In total, the entire study will take 45 days to complete.*

**On Day 1**, after the three-day co-administration training module described above, 60 households (HH) or roughly 300 people will be targeted for MDA subjects included in the study will receive concomitantly azithromycin (up to 1 g or four 250 mg tablets), ivermectin (up to 12 mg or four 3 mg tablets) and albendazole (one 400 mg tablet per included subject irrespective of height and age). This will mean that the four teams in the trial arm and the four teams in the control arm will have treated 1200 people each (300 x 4) by the end of Day 1. Teams will remain at the location of the MDA for the entire day and night on standby in case there are any immediate complaints from the targeted beneficiaries. Note that, as described in the “Intensified medical access precautions” section, a medical doctor will remain centrally located between within the woreda throughout the 14 actual days of distribution in the unlikely occurrence of a reaction to the medication.

**On Day 2**, the clinical nurses on each team, led by the three HDA members, will travel to all 60 households within their team’s catchment area to confirm that all 300 persons that received drugs on Day 1 are all healthy and to document any AEs/SAEs that may have occurred. This will also serve as opportunity for a person-to-person coverage survey for later analysis. At the end of the day, the four teams from each arm, together with the independent monitors, PI, supervisors, etc. will meet and discuss if there were any results that should cause concern. While the clinical nurses conduct the house-to-house visits, the HEWs on each team will move to the next group of 60 households targeted for the Day 3 MDA and mobilize that community.

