7.1 List of contraindications to look for: 1=Yes, 2=No

| Contraindications                                                                          | 1 | 2 |
|---------------------------------------------------------------------------------------------------|----------|----------|
| 7.1.1. Pregnancy                                                                                  |          |          |
| 7.1.2. Breastfeeding                                                                              |          |          |
| 7.1.3. Children less than 5 years of age ( $\leq 90\text{cm}$ )                                   |          |          |
| 7.1.4. Allergy to one of the study drugs: azithromycin, Ivermectin, Abendazole                    |          |          |
| 7.1.5. Medicine intake: antacids containing aluminium or magnesium, nelfinavir, ergot derivatives |          |          |
| 7.1.6. Serious illness (systemic edema, severe dyspnea, etc.)                                     |          |          |
| 7.1.7. Others.....
If others, please specify:                                                  |          |          |

DECISION REGARDING INCLUSION IN THE STUDY : 1. Yes, 2. No

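### The ** note in section 7.2, read literally, gives azithromycin plus albendazole to everyone ineligible for ivermectin, which conflicts with the protocol's other instructions for infants of 6 months and under and for pregnant women

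*Protocol*

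**What the plan says.** Section 7 opens with a drug-by-drug rule: "Standard FMOH criteria for individual agent MDA will be used to determine eligibility of individuals to receive each drug". People eligible for all three drugs are enrolled; the others are outside the study but may still be treated.

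Section 7.2 lists the exclusions. The ** mark hangs on the line "Less than 5 years of age (not eligible for ivermectin". The note it points to says "Note that patients that are not eligible for IVM, will receive azithromycin and albendazole", and adds that people given these two drugs are followed by the same procedure as triple-drug recipients, to pick up adverse events of the combination. Two other bullets concern ivermectin-ineligible groups. Pregnant women get azithromycin but neither albendazole nor ivermectin. Lactating women get azithromycin and albendazole.

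Section 2, under Azithromycin, says that "children between 6 months and 5 years old will receive syrup (200 mg per 5 ml") and that "Individuals aged 6 months and under as well as pregnant women are offered topical tetracycline".

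Section 11, in the background to the first secondary outcome, uses a different criterion in describing the azithromycin round. There, children shorter than 48 cm receive TEO. The protocol does not expand that abbreviation; I read it as tetracycline eye ointment.

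The Study Protocol Summary adds a general pointer: "Dosage and treatment age groups will follow WHO protocols" for the diseases concerned.

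**The concern.** The note is the one sentence in the eligibility section that tells teams what to give a person who cannot have ivermectin, and it is worded as mandatory. It covers children from birth to under 5 years without distinction. Because it speaks of anyone ineligible for ivermectin, it also reaches pregnant women, although its mark sits on the under-5 line.

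Two things are at stake. The first is participant protection: a team that follows the note and a team that follows section 2 would do different things for the same infant or the same pregnant woman. The second is the two-drug safety follow-up that the note itself sets up. If teams differ on who belongs in that group, its denominator varies from team to team and its adverse event proportion is hard to interpret.

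**Working it through.** The main check is textual. The table shows what each place says about each group that cannot have ivermectin.

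| Group | ** note, 7.2 | Bullets, 7.2 | Section 2, Azithromycin | Section 11 |
|---|---|---|---|---|
| 6 months and under | azithromycin + albendazole | excluded from study; no drug named | topical tetracycline | TEO if shorter than 48 cm |
| 6 months to under 5 years | azithromycin + albendazole | excluded from study; no drug named | azithromycin syrup | TEO if shorter than 48 cm |
| Pregnant women | azithromycin + albendazole | azithromycin, no albendazole | topical tetracycline | not mentioned |
| Lactating women | azithromycin + albendazole | azithromycin + albendazole | not mentioned | not mentioned |

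Reading across the rows:

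1. **6 months and under.** The note and section 2 disagree on azithromycin. They do not disagree on albendazole, because the protocol states no lower age limit for that drug.
2. **6 months to under 5 years.** The note and section 2 agree that azithromycin is given.
3. **Boundary for tetracycline.** Section 2 uses age and section 11 uses height. An infant of 6 months or less who measures 48 cm or more gets tetracycline by the first criterion and not by the second.
4. **Pregnant women.** There are three different instructions. The note adds albendazole, which the bullet rules out. The bullet gives azithromycin, where section 2 offers topical tetracycline.
5. **Lactating women.** The note and the bullet agree.

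The protocol gives no count of infants, so the size rests on an assumed share of 1.5-2% of residents aged 6 months and under. The other inputs are 42 gotes per arm (sections 8.1 and 8.8) and 190 people per gote (section 8.1, Table 2), taken here as residents.

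- Trial arm: 42 × 190 = 7,980. Then 7,980 × 0.015 = 119.7 and 7,980 × 0.02 = 159.6, so about 120-160 infants.
- Both arms: 84 × 190 = 15,960. Then 15,960 × 0.015 = 239.4 and 15,960 × 0.02 = 319.2, so about 240-320 infants.

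The trial-arm figure is the easier one to defend. The note concerns a two-drug combination, whereas the control arm receives ivermectin/albendazole and azithromycin two weeks apart. The documents give no basis for counting pregnant women, and I do not estimate that number.

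**The case against.** The best defence is that the note does not stand alone. Section 7 makes eligibility drug-specific, and the Summary ties treatment age groups to WHO protocols. Section 8.6.2 has health extension workers dose azithromycin by dose pole, and the training in section 8.2 starts from the national manual. A well-trained team may never give an infant azithromycin. This stands in part. A reader might infer that teams would treat infants against section 2, but the documents support only that the note could be read that way. The general pointers do not remove the conflict, since they refer to outside criteria while the note is the specific instruction for this group.

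Four further inferences are tempting and do not hold:

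- **That the albendazole half also breaks a protocol age rule for infants.** No such age limit is stated. For children, the conflict concerns azithromycin only.
- **That section 8.8 extends albendazole to infants.** Its wording is "albendazole (one 400 mg tablet per included subject irrespective of height and age"), and children under 5 are not included subjects.
- **That the field forms let infants through unnoticed.** Contraindication item 7.1 lists "Children less than 5 years of age" and ends in a decision on study inclusion, so infants already fail it. The recruitment and treatment forms record date of birth or approximate age, and height. Infants can be identified if the forms are completed for them.
- **That the trial result is compromised.** Infants and pregnant women are excluded, so the sample size, margin and primary comparison do not depend on the note.

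**Conclusion.** The concern holds as a contradiction between operational instructions. Taken literally, the ** note conflicts with section 2 on azithromycin for infants of 6 months and under. It conflicts with the pregnancy bullet in 7.2 on albendazole, and that bullet in turn conflicts with section 2. Section 11 adds a second, incompatible criterion for tetracycline.

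The consequences are possible contradictory treatment of these groups during drug distribution and an ill-defined two-drug follow-up group. The infant counts above depend wholly on the assumed 1.5-2% share and on 190 being the resident population of a gote; the contradiction does not depend on them. Because it bears on participant protection and is cheap to remove, it should be settled before teams are trained. Nothing here says which of the conflicting clinical instructions is correct.

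**What to change.** Before training, the sponsor's clinical team should:

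1. Reconcile section 2 (Azithromycin), the opening of section 7, the bullets and ** note of section 7.2, and the tetracycline criterion in section 11. The result should be one instruction per drug for infants and one for pregnant women, with one criterion (age or height) for tetracycline.
2. Reword the ** note so that it follows the drug-by-drug eligibility rule of section 7 and agrees with the pregnancy bullet as reconciled.
3. Keep adverse event follow-up for everyone who actually receives azithromycin plus albendazole, including lactating women and anyone dosed in error, with age recorded. Restricting follow-up to children eligible for both drugs would drop lactating women and any infant dosed in error, and so lose safety information.

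The cost is a short amendment to the wording and a training point. No additional participants, visits or staff are needed, and the sample size is unchanged.
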